#### Adherence

Medication adherence is calculated as the percentage of days covered by medication (PDC) based on pharmacy dispensing of one drug group since the start of the therapy until the end of the study period. Patients with a PDC of at least 80 % are labeled as “sufficiently adherent.” PDCs are calculated per medication group (see Appendix), except for blood glucose lowering drugs. As for diabetes, often, more than one drug is used, and patients have to adhere to each drug from the subclass, e.g. to biguanides and sulfanilamide derivatives. Data on dispensing will be based on routine pharmacy data collection.

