A measurement period of at least 8 months is preferred in order to get valid information from dispensing data. A first prescription is usually dispensed for 14 days, followed by a prescription for 90 days. After 8 months, at least two repeat prescriptions after the second dispensing must have had occurred to meet a PDC of 100 %. As we assume a PDC of 80 % is sufficient, at least (14 days + 180 days =) 196 days * 1.2 = 234 days = 7.8 months are needed to detect nonadherence. If the last patient was included after 14 months, together with the measurement period, this ends up the total study period with 22 months needed for follow up.

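### The derivation of the minimum PDC window is wrong (the break-even is 242.5 days, not 234), and the planned 8 months lies almost exactly on that break-even

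*Protocol article*

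**What the plan says.** The protocol article justifies the length of follow-up in the last paragraph of Sample size. It states a preference: "A measurement period of at least 8 months is preferred in order to get valid information from dispensing data". It then describes the usual dispensing pattern, "A first prescription is usually dispensed for 14 days, followed by a prescription for 90 days", and says that after 8 months "at least two repeat prescriptions after the second dispensing must have had occurred to meet a PDC of 100" %. From this it derives a minimum window by adding the first 14 days to 180 days and scaling the sum: "196 days * 1.2 = 234 days = 7.8 months are needed to detect nonadherence".

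The threshold that the scaling should reflect is in the Adherence section under Measures: "Patients with a PDC of at least 80 % are labeled as “sufficiently adherent". The same section runs PDC from the start of therapy to the end of the study period. The Outcomes section reads the primary outcome at 8 months. Data analysis compares PDC between arms both as a dichotomy at 80 % and as a mean.

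**The concern.** The line is meant to show that 8 months is long enough for a patient who stops collecting medication to drop below the 80 % threshold. If the minimum is understated, the margin that 8 months appears to have over it is not there.

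This matters for the dichotomous comparison because supply comes in large steps. Patients who follow the usual pattern and stop after the same dispensing all have the same number of days supplied. They therefore cross the threshold together, on the same day of follow-up. If the window ends close to that day, a small difference in how its length is counted moves the whole group from one category to the other.

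**Working it through.** **Inputs, all from the protocol article.** First dispensing 14 days, later dispensings 90 days, two repeats needed after the second dispensing (Sample size); adherent if PDC is at least 80 % (Adherence); window of at least 8 months (Sample size); outcome at 8 months (Outcomes).

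**Supply.** With both repeats collected: 14 + 90 + 90 + 90 = 284 days. Without the last repeat: 14 + 90 + 90 = 194 days. The printed 14 + 180 is this second quantity, so the sum should read 194, not 196.

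**The printed product.**
- 196 × 1.2 = 235.2
- 194 × 1.2 = 232.8
- 195 × 1.2 = 234.0

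Only 195, which the text does not contain, gives 234 exactly. The first two come within about a day of 234, and both round to 7.8 months at 30 days per month (7.84 and 7.76). If this were all, it would be a slip without consequence. The conversion itself implies a 30-day month: 234/7.8 = 30.

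**The factor.** With supply S and window T, PDC = S/T. This is below 0.80 only when T > S/0.8 = 1.25 × S. At T = 1.2 × S, PDC is 1/1.2 = 83.3 % whatever S is, so a window built with 1.2 cannot detect the case for which it was derived.

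**Corrected minimum.** 194/0.8 = 242.5 days. That is 242.5/30 = 8.08 months of 30 days, or 242.5/30.44 = 7.97 average calendar months.

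**PDC with 194 days of supply and nothing collected afterwards.**

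| Window (days) | PDC = 194/window | Label |
|---|---|---|
| 234 (printed minimum) | 82.9 % | adherent |
| 240 (8 months of 30 days) | 80.8 % | adherent |
| 242 | 80.2 % | adherent |
| 243 | 79.8 % | nonadherent |
| 244 | 79.5 % | nonadherent |
| 245 | 79.2 % | nonadherent |
| 270 | 71.9 % | nonadherent |
| 365 | 53.2 % | nonadherent |

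**Length of 8 calendar months.** Counted over start dates in 2015 and 2016, the span is 242 days for 88 of 720 dates (12 %) and 243 to 245 days for the other 632 (88 %).

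**If 196 days of supply had been meant** (an assumption; the text gives 14 and 180): 196/0.8 = 245 days, and such a patient would be at 81.7 % at 240 days and exactly 80.0 %, hence adherent, at 245.

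**Neighbouring steps.** One dispensing fewer gives 104/0.8 = 130 days, and one more gives 284/0.8 = 355 days. Only the 194-day step lies near 8 months.

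**The case against.** A reader might infer that patients who miss the last repeat will be counted as adherent in the primary analysis. The documents do not support that, for three reasons.

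- 234 days is not used as the outcome window anywhere. It is a lower bound offered in support of a longer one, at least 8 months.
- If 8 months means calendar months, 88 % of start dates give 243 days or more, and the patient is then labelled nonadherent. The corrected minimum, 7.97 average calendar months, still fits under 8. The 240-day reading is only inferred from the 30-day month in the conversion.
- If PDC runs to the end of the study, as the Adherence section says, most windows are longer still and the missed repeat is detected easily.

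The effect is also confined to one stopping pattern. The 14- and 90-day supplies are described only as usual, the documents do not say how many patients would stop at 194 days, the window rule is the same in both arms, and mean PDC is analysed as well. The 39, 56 and 112 patients per pharmacy and the 22-month study period do not rest on this line. An exact day count could reasonably be left to a fuller document.

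All of this stands, and it limits the consequence. It does not repair the derivation, and it does not restore the margin that the printed figure suggests. Nor does it settle which window applies, because the article itself gives two: 8 months, and the end of the study period.

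**Conclusion.** The derivation is wrong in its sum, its product and its factor. Of these, the factor is the one that matters: it understates the minimum window by 242.5 − 234 = 8.5 days. At the printed minimum, the patient whom the line is meant to detect has a PDC of 82.9 % and is labelled adherent.

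On the 30-day month that the line uses, 8 months appears to clear the minimum by 240 − 234 = 6 days. In fact it falls 2.5 days short. In calendar months it lies between half a day short (242) and 2.5 days beyond (245). The label given to patients with 194 days of supply therefore depends on the counting convention, which the article does not state.

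This rests on the 14- and 90-day pattern that the article gives and on no further collection within the window. The number of patients affected is unknown, so no size can be put on the misclassification. The point is a minor correction. The arithmetic is certain, and its effect is limited to the dichotomous outcome in this one group.

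**What to change.** 1. Under Sample size, replace the line with 14 + 180 = 194 days and 194/0.8 = 242.5 days.
2. State the primary PDC window as one number of days from the first dispensing, the same for every patient, and above 242.5. The smallest whole number that works is 243. Some margin is preferable, since 243 to 245 days leaves PDC within one percentage point of the threshold. A few days more moves it clear (for example 194/252 = 77.0 % at 36 weeks) without approaching the next step at 355 days.
3. Reconcile the Adherence section, which ends PDC with the study period, with Outcomes and Sample size, which use 8 months.

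The window should be set before outcome data are compared between arms, because a later choice between 240 and 244 days could relabel a whole group. The cost is a corrected line, a stated window and at most a few more days of routine dispensing data for the last patients. The sample size does not change.

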### Data analysis

The primary analysis will be an intention-to-treat analysis to test whether patients starting with cardiovascular or oral blood glucose-lowering medication who are at high risk for nonadherence and who received a tailored intervention based on the patient’s identified emotional, cognitive, and practical barriers will be more adherent compared to patients who did not receive the intervention, expressed as PDC. We will compare differences in medication adherence between the intervention and control group both as a dichotomous (PDC < 80 % versus PDC ≥ 80 %) and continuous outcome measure (mean PDC). Because patients are clustered in pharmacies, we will perform multilevel analyses, with adjustment for potential confounders (patient age, gender, diagnosis, and number of medications). Secondary analyses will test the hypothesis that patients who received the tailored adherence intervention will be more adherent compared to patients who did not receive this intervention, expressed by the ProMAS score. We will compare differences in the ProMAS score between intervention and control group both as a dichotomous (score < 13 versus ≥ 13) and continuous outcome measure (mean score). To assess differences between groups, we will perform linear and logistic mixed models. Further secondary analyses will assess the frequency of different barriers for medication adherence. We will compare differences in the profile score between intervention and control group both as a dichotomous (per barrier, present, or absent) and continuous (mean number of barriers present) outcome measure. Finally, the predictive values of the ProMAS score and the score on the eight identified barriers on patient adherence, based on dispensing data, will be quantitatively assessed. All statistical analyses will be performed using SPSS software (version 20, IBM Corp.) or MLWIN (version 2.28, University of Bristol).

We will qualitatively analyze the interviews with pharmacists and patients. The interviews will be transcribed verbatim. The transcripts will be analyzed by open coding at macro level using predefined main codes. After the open coding, the research team will group themes and subthemes for each level of healthcare. The program Atlas.ti (version 6, ATLAS.ti Scientific Software Development GmbH) will be used for analysis.

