### Sample size

For the sample size calculation, the following assumptions are made: we assume that a percentage of 60 % is nonadherent in our sample of patients at high risk based on their ProMAS score. This assumption is reasonable according to published studies [6]. We assume that the intervention will increase the 80 % PDC in the intervention group by 20 % compared to the control group. As patients are clustered within pharmacies, the evaluation will be performed by multilevel analysis to adjust for clustering. For the effect of clustering, an intracluster correlation (ICC) of 0.05 was assumed.

In agreement with conventional power calculations, a power of 80 % to detect a true difference and a chance of 5 % of a type 1 error to wrongly conclude on a difference are assumed. For this trial, in the DOH/CAZO setting, we assume that there are at least 14 community pharmacies willing to participate. The sample size calculation results in 39 patients needed per pharmacy. PASS software version 11 was used to determine the appropriate sample size. Considering 30 % lost to follow-up during the study period, 56 patients need to be included per pharmacy to achieve the power needed. If only 50 % of the patients agree to join the study, 112 patients need to be invited per pharmacy.

In the potentially participating 25 pharmacies, a total of at least 6,081 single patients with primary dispensings of cardiovascular or oral blood glucose-lowering medications were detected within 12 months (as observed in historical data). This means that, on average, 20 subjects started with cardiovascular or oral blood glucose-lowering medication monthly per pharmacy. Assuming 40 % of the starters at risk for nonadherence (determined by a ProMAS score ≥ 13), this means, on average, that eight patients are available monthly per pharmacy for an intervention. The period to have 112 starters on cardiovascular or blood glucose-lowering medication per pharmacy will be approximately 14 months.

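### The planned multilevel models carry no small-sample provision; read with a z test they give about 7 to 9 % false positives with 14 pharmacies, against the stated 5 %

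*Protocol article*

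**What the plan says.** The Data analysis section compares the arms on PDC both as a dichotomy at 80 % and as a mean. The method is given as "Because patients are clustered in pharmacies, we will perform multilevel analyses, with adjustment for potential confounders". A few sentences later, after the ProMAS comparison, it adds "To assess differences between groups, we will perform linear and logistic mixed models". The software is SPSS 20 or MLwiN 2.28. The section does not say which reference distribution gives the p-value and interval, whether models are fitted by ML or REML, or whether anything is done about the number of pharmacies.

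The Sample size section gives "a chance of 5 % of a type 1 error to wrongly conclude on a difference are assumed" together with "a power of 80 % to detect a true difference". On the number of clusters it says "we assume that there are at least 14 community pharmacies willing to participate". The Abstract says that 25 pharmacies will be randomized. The section on recruitment of pharmacies says that all 25 will be invited, that those participating are randomized within small and large strata, and that the two pilot pharmacies must be in the intervention arm.

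**The concern.** The arm is assigned to whole pharmacies, so the error term of the arm effect comes from the spread between pharmacies. With 14 pharmacies, 7 per arm, that leaves about 12 degrees of freedom. The two-sided 5 % critical value is then about 2.18 rather than 1.96. Maximum likelihood adds a second problem: it divides the between-pharmacy sum of squares by 14 instead of 12 and so understates the standard error. A multilevel model accounts for clustering but does not by itself correct either of these.

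If the output is read with the large-sample test, the deciding comparison of the trial is declared significant too often when there is no effect, and its interval is too narrow. If the choice is left open, the reference distribution can also be picked after the results are seen.

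**Working it through.** **Inputs (Sample size section).** Control arm 40 % adherent, from "we assume that a percentage of 60 % is nonadherent in our sample of patients at high risk based on their ProMAS score". Intervention arm 60 %, reading the 20 % in "the intervention will increase the 80 % PDC in the intervention group by 20 % compared to the control group" as percentage points. ICC 0.05, two-sided 5 %, power 80 %, 14 pharmacies, m = 39 analysed per pharmacy. Assumptions not in the document: 7 pharmacies per arm, ICC on the observed (0/1) scale, no covariates.

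**1. Reproducing the plan's figure.**
- Patients per arm without clustering, unpooled variance: n = (1.96 + 0.8416)² × (0.24 + 0.24) / 0.20² = 94.19.
- With design effect 1 + (m − 1) × 0.05 and k = 7 pharmacies per arm: m = n(1 − ICC) / (k − n × ICC) = 94.19 × 0.95 / (7 − 4.71) = 39.06.
- Allowing for 30 % loss: 39 / 0.7 = 55.7, so 56.

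Both figures match the protocol. Other versions do not: pooled variance gives 42.8, continuity correction 61.6, and a one-sided test 21.4. The planning therefore used normal quantiles.

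**2. Closed form for a balanced linear mixed model, z test.** The REML statistic follows t with K − 2 degrees of freedom, apart from truncation of the variance component at zero. ML inflates it by √(K/(K − 2)).
- K = 14, REML: P(|t₁₂| > 1.96) = 7.4 %.
- K = 14, ML: P(|t₁₂| > 1.96 × √(12/14)) = P(|t₁₂| > 1.81) = 9.5 %.
- K = 25, REML: P(|t₂₃| > 1.96) = 6.2 %.
- K = 25, ML: P(|t₂₃| > 1.96 × √(23/25)) = P(|t₂₃| > 1.88) = 7.3 %.

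At K = 14 the z-based interval has 1.96/2.179 = 0.90 (REML) or 0.90 × √(12/14) = 0.83 (ML) of the width of the t-based interval. Coverage is about 90.5 to 92.6 %.

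**3. Simulation under no effect.** The linear rows use 200,000 balanced data sets, with the variance truncated at zero. The logistic rows use beta-binomial data with 40 % in both arms, ML with 25-point quadrature and a Wald z test. They rest on 16,000 runs for the first row (Monte Carlo SE 0.2 points) and 4,000 for the others.

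| Pharmacies | m | ICC | Linear REML | Linear ML | Logistic ML |
|---|---|---|---|---|---|
| 14 | 39 | 0.05 | 7.3 % | 9.3 % | 9.3 % |
| 14 | 16 | 0.05 | 6.7 % | 8.3 % | 7.5 % |
| 14 | 39 | 0.01 | 5.8 % | 6.9 % | 7.1 % |
| 25 | 39 | 0.05 | 6.2 % | 7.3 % | 6.7 % |

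With 14 pharmacies of unequal size (CV 0.6, assumed) the logistic rate was also 9.3 %.

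**4. What restores 5 %.** At 14 pharmacies, m = 39 and ICC 0.05, reading the same fits against t with 12 degrees of freedom gives 5.0 % (linear REML), 6.6 % (linear ML) and 6.6 % (logistic ML). A t-test on pharmacy-level proportions gives about 5 %. So for mean PDC the degrees of freedom suffice under REML, while for the dichotomy the ML logistic model stays somewhat too liberal.

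**5. Power under the corrected test.** The standard error at m = 39 is √(2 × 0.24 × 2.9 / (7 × 39)) = 0.0714, so the standardised effect is 0.20/0.0714 = 2.80. With z, power is Φ(2.80 − 1.96) = 80.0 %. With a noncentral t on 12 degrees of freedom and critical value 2.179 it is 73.0 %. About 76 analysed patients per pharmacy would be needed for 80 %.

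**The case against.** The protocol does not state the faulty step. It names a class of model and two programs, but no Wald z test and no ML fit. The degrees-of-freedom method is commonly left to an analysis plan, and this article is condensed. REML with Satterthwaite degrees of freedom is itself a multilevel analysis and fits the text as written. The sentence naming logistic mixed models follows the ProMAS comparison, so for the primary outcome only multilevel analysis is fixed. Fourteen is a minimum; with all 25 pharmacies the excess is one to two points.

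Most of this stands, and it makes the point conditional. It also rules out three stronger readings that a reader might infer.
- **The trial will test at up to twice its stated level.** One set of 3,000 simulated trials with unequal pharmacies (CV 0.5) did give 10.4 %, but a run with greater imbalance gave 9.3 %, and the protocol gives no cluster-size variation.
- **Every between-arm interval covers only 90 to 92 %.** Linear REML covers about 92.7 % even with z, and coverage improves with more pharmacies.
- **The ProMAS and barrier comparisons are inflated to the same degree.** They use all participants and no ICC is given for them, so the size is unknown.

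Two things keep the point alive. The 39 per pharmacy is reproduced with normal quantiles, so at least the planning ignored the small number of clusters; this does not prove the same of the analysis. And for the dichotomous outcome a t reference alone leaves about 6.6 %, so the choice of model matters as well as the degrees of freedom.

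**Conclusion.** The point holds as a conditional one, and the change is recommended rather than essential. If the planned mixed models are read with a large-sample z test, the type 1 error at the plan's values is about 7 % (linear REML) to 9 % (ML, including logistic) with 14 pharmacies, and about 6 to 7 % with 24 to 25. Across the 14-pharmacy settings with smaller clusters (m = 16) or ICC 0.01 it is 5.8 to 8.3 %. Coverage of the 95 % interval at 14 pharmacies and the planning values is about 90.5 to 93 %.

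These figures assume equal arms and no covariates. Adjusting for the size stratum as a pharmacy-level covariate, which the protocol does not list, would remove one more degree of freedom. With 14 pharmacies the z-based rates would then be 7.6 % (REML) to 11.0 % (ML) by the closed form, P(|t₁₁| > 1.96) and P(|t₁₁| > 1.96 × √(11/14)).

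**What to change.** State in the Data analysis section that the p-value and 95 % interval for the primary between-arm comparison come from a small-sample cluster method.

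- **PDC of at least 80 %:** a two-stage pharmacy-level analysis on covariate-adjusted pharmacy residuals, with a t reference on the number of pharmacies minus 2 degrees of freedom, and one fewer for each pharmacy-level covariate such as the size stratum. Alternatively, a permutation test restricted to the allocations actually possible, with the two pilot pharmacies held in the intervention arm. The logistic mixed model stays as a supporting analysis.
- **Mean PDC:** REML with Satterthwaite or Kenward-Roger degrees of freedom, in software that provides them.
- **Secondary between-arm comparisons:** the same rules.

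This takes a few sentences and no new data. The price is wider intervals and less favourable p-values. With 14 pharmacies and 39 analysed patients each, power is about 73 % rather than 80 %. The protocol should say so and should state how the number of pharmacies that join changes it.

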## Discussion

This manuscript presents the protocol for a cluster-randomized clinical trial on the effectiveness of an adherence tool to improve medication adherence in starters with cardiovascular or oral blood glucose-lowering medication. A trial provides an optimal design to elucidate the effectiveness of interventions tailored to the underlying cognitive, emotional, and practical barriers to nonadherence identified for the patient. The results will provide insight in both the effectiveness of applying the medication-adherence tool and the predicting value of the ProMAS and the identified barriers for medication nonadherence. The effect of interventions to increase adherence depends on many factors. However, many approaches to improve adherence apply the one-size-fits-all-principle. By discussing the barrier profile with the patient, pharmacists can provide personalized support. An important and unique component of this study is the provision of an intervention tailored to the patient’s emotional, cognitive, and practical barriers. Not only the intervention itself, but also the implementation of the intervention will be tailored. The research team will visit all participating pharmacies to tailor the workflow concept as much as possible to existing work procedures. As the information on the barriers and the intervention is shared among the healthcare providers, all information supplied to the patient is consistent. A limitation of our study is that the questionnaire on barriers related to nonadherence has not been extensively used and validated in earlier studies. Furthermore, randomization occurs at the pharmacy level. Therefore, GPs may have patients in both the intervention and control group, which could lead to contamination. However, the barriers are discussed with the patients in the intervention pharmacies only. As the GPs will only follow a part of the intervention from the implementation guide for those patients that are announced by the intervention pharmacists, this limitation is presumably not severe. This study will be carried out in the DOH/CAZO care groups. These care groups have innovative mindsets. Consequently, the implementation of the intervention in other care groups might need additional guidance. Within these care groups, recruitment bias may be caused by the response of patients with certain characteristics, including medication adherence. Due to privacy legislation, the characteristics of nonresponders will not be analyzed.

